### 8.3.1 Study flowchart

[figure not shown]

The end of treatment is defined as the day of the last radiation session. Follow-up time is calculated as time passed since the end of treatment. The first moment of follow-up is 3 months after end of treatment. For each follow-up moment, it is preferred to send the questionnaires and collect data as soon as possible, but a delay of maximum 6 weeks is also allowed and will not affect study progress.

### 8.4 Withdrawal of individual subjects

Subjects can leave the study at any time for any reason if they wish to do so without any consequences. The treating physician can decide to withdraw a subject from the study for urgent medical reasons.

#### 8.4.1 Specific criteria for withdrawal (if applicable)

- The patient or its legal representative request that the patient will be withdrawn from the study.

- The sponsor decides to discontinue the study due to significant safety or efficacy concerns.
- The patient becomes pregnant.
- The treating physician withdraws the patient from the study. This decision can be made because of progressive disease, toxicity or patient's inability to be exposed to the study treatment. Since early termination is one of the outcomes of this study, we will not exclude the patient from data-analysis if not explicitly requested by the patient or treating physician.

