## 8. METHODS

### 8.1 Study parameters/endpoints

#### 8.1.1 Main study parameter/endpoint

The primary outcome parameter is compliance (non CDLT) rate to the proposed cisplatin scheme. Compliance to chemotherapy is defined as the absence of CDLT. CDLT is defined as any toxicity resulting in a cisplatin dose-reduction of  $\geq 50\%$ , a postponement of treatment of  $\geq 4$  days or a definite termination of cisplatin after the first or second cycle of therapy. For weekly cisplatin regimens CDLT is defined as skipped cisplatin treatments or a definite termination of cisplatin before all scheduled cycles of therapy are given.

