### **8.6 Follow-up of subjects withdrawn from treatment**

Follow-up consists of (clinical) examination according to the national guidelines for at least 24 months after end of treatment. The researcher will collect data as previously described.

Follow-up data will be collected using EPR for withdrawn patients as well, when they were initially included, to prevent bias.

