### 10.1 Primary study parameter(s)

The primary outcome parameter is compliance (non CDLT) rate to the proposed cisplatin scheme in the intention-to-treat population.

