### 10.2 Secondary study parameter(s)

Treatment toxicity is assessed with the Common Toxicity Criteria Adverse Events (CTCAE) v5.0 for a period of 24 months from the end of treatment. Toxicity scored as CDLT by the treating physician will be assessed, clarified if necessary, and reconfirmed separately. A severe toxic event is defined as a toxicity assessed as grade 3–5. Toxicities are classified as acute if they first appeared during or up to 3 months after treatment, and are classified as late if they persist, or first appear, more than 3 months after treatment. Multiple occurrences of events of a single toxicity type within an analysis time period are counted as a single event. Median numbers of toxicity events per patient (short-term [acute] toxicity and adverse long-term [late] effects, based on the TAME method of reporting toxicities) are compared between trial arms using t-tests. Proportions of patients affected by one or more toxicity event are compared between trial arms using Fishers exact test. Total administered cisplatin dose will also be recorded and means (or medians depending on the distribution) compared between trial arms.

Overall survival, disease-specific survival, loco-regional recurrences and time to recurrence are measured from the starting date of chemotherapy and compared between the three groups by the log-rank test with all-cause mortality in the intention-to treat population. Deaths are classified as being due to head and neck cancer or to other causes. Recurrences can be loco-regional or distant, or both. Patients who died from head and neck cancer causes as the first event are classed as recurrences. Patients on follow-up and patients lost to follow-up are censored at the last date at which they were known to be alive. Total time of follow-up per patient is two years. Hazard ratios and 95% CIs are generated with a univariate Cox proportional hazards model. The Schoenfeld residuals are tested by plotting the observed Kaplan- Meier values against the Cox predicted values. The effect of randomised treatment on outcome is also assessed after adjusting for known prognostic factors with a multivariate Cox proportional hazards model. At 3 months after treatment semi-structured interviews are conducted to obtain a better understanding of the patients' experience and preference for the treatment schemes, until saturation is reached. Semi-

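### The exclusion clause in Protocol 8.4.1 lets the unblinded treating physician have a withdrawn patient removed from the analysis, which conflicts with the intention-to-treat primary analysis in 10.1

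*Protocol*

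**What the plan says.** **Analysis set.** Section 10.1: "The primary outcome parameter is compliance (non CDLT) rate to the proposed cisplatin scheme in the intention-to-treat population". Section 10.2 names the same population for survival and recurrence.

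**Withdrawal and exclusion.** Section 8.4.1 allows the treating physician to withdraw a patient: "This decision can be made because of progressive disease, toxicity or patient's inability to be exposed to the study treatment". It then recognises that early termination is itself a study outcome, and for that reason keeps withdrawn patients by default: "we will not exclude the patient from data-analysis if not explicitly requested by the patient or treating physician".

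**Primary event.** Section 8.1.1: "CDLT is defined as any toxicity resulting in a cisplatin dose-reduction of" 50% or more, in a delay of at least four days, or in definite termination after cycle one or two. For the weekly schedule, the event is a skipped administration or termination before all scheduled cycles are given.

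**Who knows and who scores.** Section 8.2 states that nobody is blinded. Section 10.2 has the treating physician score CDLT, with separate reconfirmation.

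**Data on withdrawn patients.** Section 8.6: "Follow-up data will be collected using EPR for withdrawn patients as well, when they were initially included, to prevent bias".

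**Time-to-event rules.** In section 10.2 overall survival, disease-specific survival and the recurrence endpoints "are measured from the starting date of chemotherapy". The censoring rule is: "Patients on follow-up and patients lost to follow-up are censored at the last date at which they were known to be alive".

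**The concern.** An intention-to-treat analysis keeps every randomised patient in the arm to which they were allocated. The exception in 8.4.1 gives a clinician the right to take a randomised patient out. Three features make this more than loose wording.

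- **The trigger overlaps the endpoint.** A patient whose cisplatin is stopped early for toxicity is non-compliant under 8.1.1. The same patient qualifies for physician withdrawal, and so for a request to be excluded.
- **The person making the request knows the arm** and has already scored the event.
- **Nothing limits the request.** The clause sets no grounds, no deadline and no independent review.

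If requests fall unevenly between the arms, the comparison is biased on the primary endpoint of a trial with 70 randomised patients. The clause also undercuts the aim of 8.6, since data collected on withdrawn patients to avoid bias could then be left out of the analysis.

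A lesser issue concerns the secondary endpoints. Under 10.2 a randomised patient who never starts cisplatin has no time zero, and time to recurrence is censored on the date last known alive even if disease was last assessed earlier.

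**Working it through.** **1. Inputs.** From section 4.4: compliance 55.7% (three-weekly) and 86.3% (weekly), two-sided alpha 0.05, power 80%, 33 per arm, 5% drop-out, 70 in total. From section 8.2: 1:1 allocation, so 35 per arm. From section 10: Fisher's exact and Pearson chi-square tests are both named. The number of excluded patients, k, is not in the documents and is an assumption, shown as a range.

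**2. The plan's own figure.** n = [1.960·√(2·0.710·0.290) + 0.842·√(0.557·0.443 + 0.863·0.137)]² / 0.306² = 33.3 per arm. This rounds up to 34, against the stated 33, where power is 79.6%. For drop-out, 66/0.95 = 69.5, so 70. The sample size is reproduced within rounding and is not at issue.

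**3. Scale for k.** 5% of 70 is 3.5 patients over both arms. With 55.7% compliance, about 35 × 0.443 = 15.5 patients per arm are non-compliant, so k = 3 is about a fifth of them.

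**4. Type I error.** True compliance is 55.7% in both arms, with 35 per arm. For every pair of binomial outcomes, k non-compliant patients (or all, if fewer) are removed from the weekly arm, the test is applied at 0.05 two-sided, and the probabilities of the rejecting tables are summed.

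| k removed, weekly arm only | Chi-square | Fisher |
|---|---|---|
| 0 | 4.5% | 2.6% |
| 1 | 5.6% | 3.7% |
| 3 | 8.0% | 6.3% |
| 5 | 14.4% | 12.6% |

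(The chi-square value at k = 3 is 8.05% to two decimals.)

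**5. A borderline table.** Three-weekly 20/35 against weekly 28/35. Chi-square: z = (0.800 − 0.571)/√(0.686·0.314·2/35) = 2.06, p = 0.039.
- Remove one non-compliant three-weekly patient (20/34): chi-square p = 0.056; Fisher stays at 0.070.
- Remove one non-compliant weekly patient (28/34): chi-square p = 0.023; Fisher goes from 0.070 to 0.036.

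One removal can cross 0.05 here, in a direction that depends on the arm and the test.

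**6. A table near the planned rates.** Three-weekly 20/35 against weekly 30/35 (expected counts 19.5 and 30.2), removing non-compliant three-weekly patients:

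| Removed | Chi-square p | Fisher p |
|---|---|---|
| 0 | 0.008 | 0.016 |
| 1 | 0.012 | 0.016 |
| 2 | 0.019 | 0.028 |
| 3 | 0.029 | 0.048 |
| 4 | 0.045 | 0.082 |

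Four removals leave the chi-square result significant and are what it takes to lose significance by Fisher.

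**7. Time origin and censoring.** Section 8.2 places randomisation after consent. The documents give neither the interval to first cisplatin nor the share who never start, and not the gap between last disease assessment and last contact. No figure can be derived.

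**The case against.** **The default is to keep patients.** This is true: 8.4.1 keeps them because early termination is an outcome, and 8.3 says data remain usable after CDLT and a change of therapy. Section 8.4 speaks of urgent medical reasons for physician withdrawal, and 10.2 has CDLT reconfirmed. These safeguards make heavy use of the clause unlikely. They do not remove it: 8.4.1 lists broader grounds, and reconfirming an event does not protect against leaving the patient out.

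**A patient's own request is legitimate.** Agreed. That is a matter of consent, and the defect is only the physician's right.

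**One request could overturn the trial.** A reader might infer this from step 5. It holds only for a borderline result, as step 6 shows. The larger inflation in step 4 assumes several removals, all in one arm.

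**Section 8.6 contradicts 8.4.1.** A reader might say so, but 8.6 governs data collection, not the analysis set. Complete collection would even allow an analysis of all randomised patients. The clause weakens the stated purpose of 8.6 without contradicting its text.

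**Survival becomes an analysis of patients who started treatment.** A reader might infer this from the clock. Section 10.2 does not say that never-starters are dropped; it says intention-to-treat and leaves their time zero undefined. Chemotherapy start is also an origin shared with the non-randomised normal-SMM group, which takes part in the three-group comparison.

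**Endpoint-specific censoring is commonly left to an SAP.** This is fair. Visits every two and then three months (section 3) should also keep the gap short for patients still in follow-up.

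**Conclusion.** The concern holds for the exclusion clause. Section 8.4.1 permits an unblinded physician to have a patient removed for reasons that overlap the primary event, and this cannot be squared with the intention-to-treat analysis in 10.1. Because the protocol states the rule outright, an SAP would have to override it.

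The size depends on use that cannot be known in advance. One removal from the weekly arm adds about 1.1 percentage points to the type I error by either test. Three take it to 8.0% (chi-square) or 6.3% (Fisher), above the planned 5%. These figures assume 35 per arm, equal true compliance of 55.7%, and removals of non-compliant patients from one arm only. Near the planned effect, the conclusion withstands up to three removals from the three-weekly arm by either test.

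The time origin and the recurrence censoring are real but secondary. They touch no primary result, cannot be quantified from the documents and are probably small.

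**What to change.** **Main change (8.4.1).** Delete the treating physician from the exclusion clause. State that only a patient's own withdrawal of consent for data use removes data, and only as far as that consent requires. State in 10.1 that every randomised low-SMM patient is analysed as allocated. The physician's authority over treatment is untouched.

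**Lower priority (10.2).** For the comparison of the two randomised arms, measure overall survival and time to recurrence from randomisation. Chemotherapy start may stay as the origin for the three-group comparison with the normal-SMM patients. Censor time to recurrence at the last disease assessment, and keep the date last known alive for overall survival.

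**Cost.** A few words in 8.4.1, 10.1 and 10.2, in one amendment. No added patients or visits: the sample size of 70 is unchanged, and with no removals the type I error in step 4 is within the planned 5% for both tests.

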### **8.5 Replacement of individual subjects after withdrawal**

N.A.

### **8.6 Follow-up of subjects withdrawn from treatment**

Follow-up consists of (clinical) examination according to the national guidelines for at least 24 months after end of treatment. The researcher will collect data as previously described.

Follow-up data will be collected using EPR for withdrawn patients as well, when they were initially included, to prevent bias.

### **8.7 Premature termination of the study**

This study will be terminated prematurely when new scientific evidence emerges making this study redundant.

## **9. SAFETY REPORTING**

### **9.1 Temporary halt for reasons of subject safety**

In accordance to section 10, subsection 4, of the WMO, the sponsor will suspend the study if there is sufficient ground that continuation of the study will jeopardise subject health or safety. The sponsor will notify the accredited METC without undue delay of a temporary halt including the reason for such an action. The study will be suspended pending a further positive decision by the accredited METC. The investigator will take care that all subjects are kept informed.

### **9.2 AEs, SAEs and SUSARs**

#### **9.2.1 Adverse events (AEs)**

Adverse events are defined as any undesirable experience occurring to a subject during the study, whether or not considered related to the intervention. Adverse events classified according to the CTCAE criteria as grade 3 or higher, reported spontaneously by the subject or observed by the investigator or his/her staff and will be recorded. We do expect adverse events in this study, since this is common during cisplatin treatment, especially in a high-dose.

#### **9.2.2 Serious adverse events (SAEs)**

A serious adverse event is any untoward medical occurrence or effect that occurs that:

- results in death;
- is life threatening (at the time of the event);
- requires extra hospitalisation or prolongation of existing inpatients' hospitalisation;
- results in persistent or significant disability or incapacity;
- is a congenital anomaly or birth defect; or
- any other important medical event that did not result in any of the outcomes listed above due to medical intervention but could have been, based upon appropriate judgement by the investigator.

The population of the present study consists of patients who are treated for HNSCC. Adverse events are relatively common in this population, and are expected to be related to their disease and treatment of the disease, not to participation in this study. Therefore the following events will not be reported as SAE and/or AE:

- an elective hospital admission;
- nausea (CTCAE v5.0 grade 1 through 3)
- mucositis (grade 1 through 3);
- acute kidney injury and/or electrolyte disbalances (grade 1 through 3);
- diarrhea (grade 1 through 3);

This study is expected to pose a negligible risk for patients; any serious adverse events occurring during the study period are expected to be related to the standard treatment and not to the study intervention. Because of this, SAEs that result in death or are life threatening will

be not reported expedited through the webportal Toetsingonline to the accredited METC that approved the protocol. The SAE's will be documented by the investigator and will be reported once a year.

### **9.2.3 Suspected unexpected serious adverse reactions (SUSARs)**

Adverse reactions are all untoward and unintended responses to an investigational product related to any dose administered.

Unexpected adverse reactions are SUSARs if the following three conditions are met:

1. the event must be serious (see chapter 9.2.2);
2. there must be a certain degree of probability that the event is a harmful and an undesirable reaction to the medicinal product under investigation, regardless of the administered dose;
3. the adverse reaction must be unexpected, that is to say, the nature and severity of the adverse reaction are not in agreement with the product information as recorded in:
  - Summary of Product Characteristics (SPC) for an authorised medicinal product;

The sponsor will report expedited the following SUSARs through the web portal *ToetsingOnline* to the METC:

- SUSARs that have arisen in the clinical trial that was assessed by the METC;
- SUSARs that have arisen in other clinical trials of the same sponsor and with the same medicinal product, and that could have consequences for the safety of the subjects involved in the clinical trial that was assessed by the METC.

The remaining SUSARs are recorded in an overview list (line-listing) that will be submitted once every year to the METC. This line-listing provides an overview of these SUSARs from the study medicine, accompanied by a brief report highlighting the main points of concern. The expedited reporting of SUSARs through the web portal Eudravigilance or ToetsingOnline is sufficient as notification to the competent authority.

The sponsor will report expedited all SUSARs to the competent authorities in other Member States, according to the requirements of the Member States.

The expedited reporting will occur not later than 15 days after the sponsor has first knowledge of the adverse reactions. For fatal or life threatening cases the term will be maximal 7 days for a preliminary report with another 8 days for completion of the report.

## **9.3 Annual safety report**

In addition to the expedited reporting of SUSARs, the sponsor will submit, once a year throughout the clinical trial, a safety report to the accredited METC, competent authority, and competent authorities of the concerned Member States.

This safety report consists of:

- a list of all suspected (unexpected or expected) serious adverse reactions of grade 3 or higher according to CTCAE v5 criteria, along with an aggregated summary table of all reported serious adverse reactions, ordered by organ system, per study. We will not report events that are mentioned in the SPC, since adverse events in cisplatin therapy are very common and related to standard of care, not to this study;
- a report concerning the safety of the subjects, consisting of a complete safety analysis and an evaluation of the balance between the efficacy and the harmfulness of the medicine under investigation.

#### **9.4 Follow-up of adverse events**

All AEs of grade 3 or higher defined according to CTCAE criteria and not excluded by the list mentioned in 9.2.2, will be followed up by the researcher until they have abated, until a stable situation has been reached or until the study has ended. Depending on the event, follow up may require additional tests or medical procedures as indicated, and/or referral to the general physician or a medical specialist. Follow-up of adverse events will be according to standard hospital procedures. The investigator will collect the information using the EPR. SAEs need to be reported till end of study within the Netherlands, as defined in the protocol

#### **9.5 [Data Safety Monitoring Board (DSMB) / Safety Committee]**

NA, see 13.2

## 10. STATISTICAL ANALYSIS

Categorical data will be represented as a number and percentage of the total. Data analysis will be performed using statistical software R and SPSS Statistics. A test for normality (Kolmogorov-Smirnoff test) and histograms will be used to assess whether continuous variables are normally distributed. Continuous data will be represented as mean  $\pm$  standard deviation (SD) if normally distributed, and median  $\pm$  interquartile range (IQR) if skewed. Fisher's exact tests, Pearson Chi square tests, independent sample t-tests and Mann-Whitney U tests will be used to assess group differences. All analyses will be two-sided and  $p < 0.05$  is considered significant. Missing data will be handled using multiple imputation, if needed; we only expect few missing data to occur due to the nature and scale of the study.

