#### 4.4 Sample size calculation

In the retrospective study by Wendrich et al., out of 112 patients 30.4% experienced CDLT (meaning compliance to chemotherapy regimen was 69.6%). Using a cut-off 43.2 cm^2/m^2, 54.5% patients had low SMM. Patients with low SMM experienced CDLT more frequently than patients with normal SMM (44.3% vs. 13.7%,  $p < 0.001$ ). Thus compliance rates to chemotherapy regimen were 55.7% and 86.3%, respectively. We hypothesize therefore that in patients with low skeletal muscle mass and weekly low dose cisplatin, also 86.3% compliance will be reached. If we compare this compliance to an expected compliance of 55.7% in the arm of with a three-weekly high dose cisplatin, 33 patients with low SMM per arm are needed to show that the compliance in the weekly low dose cisplatin scheme is statistically significantly better than the threeweekly high dose scheme (two-sided alpha 0.05 and power 80%). With an expected drop-out of 5% 70 patients with low SMM are needed. Power calculations were done using PASS software. Since 54.5% of patients undergoing cisplatin based concurrent CRT have low SMM, to find the 70 patients with low SMM a total of 129 LA-HNSCC patients undergoing cisplatin based concurrent CRT are needed.

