## 8.2 Randomisation, blinding and treatment allocation

When the patient has signed informed consent, patients with low SMM will be randomised by the investigator for three-weekly high dose (three cycles 100mg/m^2) or weekly low dose cisplatin (seven cycles 40mg/m^2). Allocation is performed by a central office on-site computer combined with allocations kept in a locked, unreadable computer file that investigators can assess only after the characteristics of an enrolled patient are entered. A stratified permuted-block procedure will randomise patients to the groups on a 1:1 ratio. Strata comprises center and two groups according to AJCC staging:

- 1) Stage I-III
- 2) Stage IV.

Neither patients, investigators nor office personnel are blinded to the group chosen by the allocation procedure.

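### Allocation is stratified by centre and stage but no analysis names these factors, and of the two tests of proportions that section 10 permits, only the uncorrected Pearson test delivers the stated 80% power

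*Protocol*

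**What the plan says.** **Allocation.** Protocol section 8.2: "A stratified permuted-block procedure will randomise patients to the groups on a 1:1 ratio. Strata comprises center and two groups according to AJCC staging" (I-III versus IV). Section 3 names five centres, so there are up to 10 strata.

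**Sample size.** Section 4.4 compares an "expected compliance of 55.7% in the arm of with a three-weekly high dose cisplatin" with the hypothesis that under the weekly scheme "also 86.3% compliance will be reached". It concludes that "33 patients with low SMM per arm are needed" at "two-sided alpha 0.05 and power 80"%, and then: "With an expected drop-out of 5% 70 patients with low SMM are needed". It does not say for which test.

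**Analysis.** Section 10 gives one general list: "Fisher's exact tests, Pearson Chi square tests, independent sample t-tests and Mann-Whitney U tests will be used to assess group differences". Section 10.1 states the primary outcome and the intention-to-treat population, but no test. Section 10.2 names Fisher's exact test for the proportion of patients with a toxicity event, a log-rank test with no mention of strata, and then: "Hazard ratios and 95% CIs are generated with a univariate Cox proportional hazards model". It adds a multivariable Cox model for the time-to-event outcomes, adjusted for prognostic factors that it does not list. Neither centre nor stage is named in section 10.

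**The concern.** There are two linked issues.

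First, blocking within centre and stage balances the arms on these factors. If the factors predict the outcome, a test that ignores them overstates the variance of the treatment difference. It then rejects too rarely under the null and gives up power that the design has already secured. Centre may well matter here, because section 5.1 leaves supportive care to local standard, although the protocol gives no figure for such an effect.

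Second, section 10 offers two tests for a binary outcome without saying which one decides the primary comparison. At about 33 per arm they differ materially in power, and section 4.4 can be right for only one of them. The trial is open-label with a single primary comparison, so the choice should be fixed before any outcome data are seen.

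**Working it through.** **Inputs.** p1 = 0.557, p2 = 0.863, two-sided alpha 0.05, power 80%, 33 per arm, 5% drop-out (all section 4.4). Allocation is 1:1 within centre by stage (section 8.2), with five centres (section 3).

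**Step 1: reproduce the stated size.** With the pooled variance, the mean rate is (0.557 + 0.863)/2 = 0.71 and the difference is 0.306.

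n = [1.96·√(2·0.71·0.29) + 0.842·√(0.557·0.443 + 0.863·0.137)]² / 0.306² = [1.258 + 0.508]² / 0.0936 = 33.3 per arm.

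The formula power at 33 is 79.6%. The unpooled version gives 30.6 per arm and the continuity-corrected version 39.6. Enumerating every possible 2×2 table, the uncorrected Pearson test has 79.9% power at 32 per arm and 81.5% at 33. The stated 33 is therefore the size for the uncorrected Pearson (Z) test. Drop-out: 66/0.95 = 69.5, so 70 patients. The plan's figures reproduce.

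**Step 2: the other permitted test.** The same enumeration, rejecting when two-sided p < 0.05:

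| n per arm | Pearson, uncorrected | Fisher's exact |
|---|---|---|
| 33 | 81.5% | 71.7% |
| 35 (all 70 analysed) | 82.8% | 75.6% |
| 38 | 86.4% | 80.4% |

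Fisher's test first reaches 80% at 38 per arm, which is 76/0.95 = 80 randomised. The Yates-corrected chi-square also has 71.7% at 33. At 33 per arm Fisher's test never rejects when Pearson's does not, so under the design rates the two disagree in 81.5 − 71.7 = 9.8% of trials.

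**Step 3: the strata.** Simulation with 66 patients, 5 centres × 2 stages and permuted blocks of 4 (block size assumed). Overall rates are held at 55.7% and 86.3%, because those are the rates on which section 4.4 is based. The protocol gives no stratum effects, so these are assumed: none; moderate (centre SD 0.7 and stage difference 0.8, both on the log-odds scale); strong (1.2 and 1.5). Ranges cover repeat runs.

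| Assumed stratum effect | Unstratified Pearson | CMH, uncorrected | CMH, continuity-corrected |
|---|---|---|---|
| None | 80–82% | 79–80% | 69–70% |
| Moderate | 82% | 83–84% | 73% |
| Strong | 83% | 87–88% | 78–79% |

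Under the null, the type I error of the unstratified test falls from about 5% with no stratum effect to 4.1–4.5% (moderate) and 3.0–3.4% (strong). The uncorrected CMH test stays at 4–5% throughout.

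**The case against.** **The stated power is not wrong.** A reader might infer from the Fisher figure that the 80% in section 4.4 is an error. The protocol does not support that. Pearson's test stands in the same sentence as Fisher's, position in a general list assigns nothing, and Fisher's test is tied only to toxicity proportions. This objection stands in full: 72% is what the trial would have *if* Fisher's test were used.

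**The strata cost no power against the plan.** A reader might also infer that ignoring the strata erodes the 80% further. That appears only if 55.7% and 86.3% are treated as rates within an average stratum, because the overall difference then shrinks, and the stratified test loses power too. With overall rates held as planned, the unstratified test keeps 80% or more. This also stands. What is lost is a possible gain, and the error is in the conservative direction.

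**The secondary outcomes are partly covered.** The multivariable Cox model may include stage. It is therefore too strong to say that no planned analysis could use the strata; the accurate statement is that none names them.

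**The statistical analysis plan may settle it.** It may name the primary test and handle the strata. But the protocol does list methods, and an analysis plan that chose Fisher's test would comply with section 10 while missing the power promised in section 4.4.

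**Fisher protects the error rate.** At 33 per arm, with common rates of 55.7% to 86.3%, Pearson's exact type I error is 5.3–6.2% and Fisher's 1.8–3.4%. The small excess is real, but Fisher's test pays for its protection with about 10 points of power.

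**CMH is sparse here.** With 66/10, or about 6.6 patients per stratum, the form of the test matters. A continuity correction would bring back a loss like that of Fisher's test. This stands, and the fix must exclude the correction.

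**Conclusion.** The point holds in a limited form. The randomisation factors are named in no analysis, and the primary comparison is left open between two tests of which only one matches the sample size. The arithmetic in section 4.4 is sound for the uncorrected Pearson test (81% exact). With Fisher's exact test, power would be 72%, or 76% with all 70 analysed. These figures rest only on the protocol's own rates.

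Leaving out the strata does not threaten validity and does not take power below 80%. When centre and stage predict CDLT, it makes the test conservative (type I error about 3% under strong effects) and forgoes about 1 point of power under moderate and about 4 under strong effects. Those figures rest on assumed stratum effects, since the protocol gives none. The change should be made because it is cheap and fixes the primary test in advance, not because the design fails without it.

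**What to change.** - **Section 10.1:** name the primary test as a Cochran-Mantel-Haenszel test without continuity correction, stratified by centre and AJCC stage group. Include a pre-set rule for pooling very small strata. Report a stratified risk difference with 95% CI.
- **Section 10.1, with 4.4:** state that neither Fisher's exact test nor any continuity-corrected test is used for the primary comparison, and name in 4.4 the test behind the 33 per arm. If an exact check is wanted, use an unconditional one such as Boschloo's test. If Fisher's test is kept as primary, restate the power in 4.4 as about 72% (76% with all 70 analysed).
- **Section 10.2:** stratify the log-rank and Cox comparisons of the two randomised arms by the same factors.

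The cost is a few sentences, with no added patients or data. The downside is about 2 points of power if centre and stage turn out to be unrelated to CDLT.
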